### Sample size and power calculation

One hundred two dyads are needed for this study considering 51 male patients enrolled in the Division of Urologic Cancer Surgery and 51 female patients enrolled in the Division of Breast Surgery at IEO in Milan.

The variable “compliance with therapy” measured by ADQ (DiMatteo et al., 1993), including the subscales Interpersonal Aspects of Care (range: from 8 to 40) and Subjective Norms (range: from −18 to 18), was used as the primary outcome of interest in the sample size calculation. The hypothesis is that the involvement of caregivers increases the patient's adherence to treatment recommendations, which in turn directly impacts the patients' prognosis as widely demonstrated in the literature (Ricci-Cabello et al., 2020). The sample size calculation was based upon the assumption that we will observe a difference of 3 points in the average values of the two subscales IAC and SN, in favor of the intervention group. A standard deviation of ~5 points is assumed for both subscales (untransformed values) according to data presented by DiMatteo et al. (1993), leading to a hypothesized effect size of 0.6. This effect size should be considered as a medium-large effect according to Cohen (2013), and it is considered to provide clinical relevance. A two-sample *t*-test will be used to compare the mean subscale values in the intervention group vs. control group. With a 1:1 randomization ratio, a total of 88 patients (44 in the intervention group and the 44 in the control group) are required to provide 80% power to detect a difference ≥ 3 points, with a type I error of 5% (two-sided *t*-test). Assuming a drop-out rate at 6-months of ~15%, a total of 102 patients will be required.

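### Two ADQ subscales form the primary outcome, but the 88 patients, 5% error and 80% power are those of one t-test, and no rule links the two tests

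*Protocol article*

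**What the plan says.** All of this stands in the protocol article under Sample size and power calculation. The ADQ variable for compliance with therapy "was used as the primary outcome of interest in the sample size calculation", "including the subscales Interpersonal Aspects of Care (range: from 8 to 40) and Subjective Norms (range: from −18 to 18" points). The assumed effect is "a difference of 3 points in the average values of the two subscales IAC and SN" in favour of the intervention. On spread: "A standard deviation of ~5 points is assumed for both subscales (untransformed values"), "leading to a hypothesized effect size of 0.6". A two-sample t-test "will be used to compare the mean subscale values in the intervention group vs. control group". The 88 patients, 44 per arm, "are required to provide 80% power to detect a difference" of at least 3 points, "with a type I error of 5% (two-sided *t*-test").

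So the section names two subscales, with one type I error, one power and one sample size. Neither this section nor Data analyses gives an either-or-both rule, a test order, a composite score or a division of the 5%. Data analyses speaks only of scales of interest and, in the singular, of a main outcome.

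**The concern.** With two primary comparisons, the error rate and the power of the primary claim depend on how the two results are combined. If a significant result on either subscale counts as success, there are two chances of a false positive and the error exceeds 5%. If both must be significant, the error stays at or below 5%, but the trial must succeed twice and power drops below the single-test figure. The sample size allows for neither.

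At stake is the claim of efficacy on adherence. With no rule fixed, the subscale that carries the claim could be chosen after the results are known, and no later analysis can repair that.

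**Working it through.** **Inputs from the article:** difference 3, SD 5, two-sided alpha 0.05, power 80%, 1:1 allocation, 44 per arm. **Assumed:** correlation r between IAC and SN, and hence between the two test statistics, from 0 to 0.7. The article gives no value.

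**1. The plan's own figure.** Effect size = 3/5 = 0.6. Per arm, n = 2 × (1.96 + 0.842)² / 0.6² = 43.6, rounded up to 44, so 88 in total. This matches exactly, for one test at an undivided 5%. The exact t-test power at 44 per arm is 79.5%, which is about 80%.

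**2. Could it be one averaged score?** The average of two scores that each have SD 5 has SD 5 × √((1 + r)/2). A 3-point difference would then be an effect of 0.85 at r = 0, 0.69 at r = 0.5 and 0.65 at r = 0.7. The stated 0.6 is the single-subscale value and would require r = 1. The separate ranges and the SD given for both subscales also point to two comparisons.

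**3. Either subscale suffices, each at 5%.** Family-wise error = 1 − P(|Z1| < 1.96 and |Z2| < 1.96). At r = 0 this is 1 − 0.95² = 9.75%. For r > 0 it comes from the bivariate normal distribution.

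**4. Both required, each at 5%.** Take a true difference of 3 points on each subscale and power of 0.795 for each. At r = 0 joint power is 0.795² = 63.2%. For r > 0 it again comes from the bivariate normal distribution.

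**5. Two equal subscales with the error controlled.** The t-test power at alpha 0.025 and 44 per arm is 70.3%. This is the Bonferroni figure and the lower bound for Holm. Holm gains because, once one subscale passes 2.5%, the other is tested at 5%. At r = 0, with both differences 3 points:
- per subscale: 0.703 + (0.795 − 0.703) × 0.703 = 0.77
- at least one subscale: 1 − (1 − 0.703)² = 0.91

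The Holm values for r > 0 were simulated with t critical values.

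| r | Error, either at 5% | Joint power, both at 5% | Holm: power per subscale | Holm: power for at least one |
|---|---|---|---|---|
| 0 | 9.8% | 63% | 77% | 91% |
| 0.5 | 9.1% | 68% | 76% | 85% |
| 0.7 | 8.4% | 71% | 75% | 81% |

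**6. Patients needed to keep 80%** (normal approximation, evaluable patients, against the planned 88):
- 2.5% for each subscale, 80% per subscale: 53 per arm, 106 in total.
- Both required, 80% joint power: 58 per arm (116) at r = 0, 55 (110) at r = 0.5 and 53 (106) at r = 0.7.
- Fixed order or one named primary subscale: 44 per arm (88), with the power applying to the first subscale only.

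**The case against.** Three objections carry weight.

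First, a reader might infer that the stated 5% and 80% can never hold together in this trial. The documents do not support that. It is true of the two unadjusted readings only. A fixed order keeps 5% and the single-test power at 88 patients. Even a rule under which either subscale suffices can meet both figures: with Bonferroni or Holm the error is at most 5%, and the power for at least one subscale is about 81% to 91% if both true differences are 3 points. The defect is that no such rule is tied to the stated figures, not that none exists.

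Second, the text never says outright that each subscale will be declared significant at 5%. This stands, and the point therefore says that the calculation implies it: 88 is reproduced only with an undivided 5%. The looser reading, a single averaged score, does not fit the stated effect size of 0.6.

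Third, multiplicity rules are often placed in an analysis plan or a full protocol, and neither is shown. Absence alone would indeed be no finding. Here, however, the article itself fixes the error rate, power and sample size for a two-part primary outcome, and whether those figures are correct depends on the missing rule.

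**Conclusion.** The point holds in this form: two subscales are primary, the sample size and its error and power belong to one test, and nothing links the two tests. With each subscale at an unadjusted 5%, the false-positive rate of the primary claim is about 8% to 10% if either suffices, or joint power is about 63% to 71% at 44 per arm if both are required.

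The power figures assume that the article's 3-point difference and SD of 5 are true for both subscales, and all ranges assume a correlation of 0 to 0.7. A higher correlation narrows the gap: at 0.9, on the normal approximation, the error is 7.0% or the joint power 75.4%. The gap closes only at perfect correlation.

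It would go too far to conclude that the trial is invalid or too small. The single-subscale arithmetic is sound, and prespecification restores the stated figures without any change to design, data collection or sample size.

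**What to change.** Add one or two sentences to Sample size and power calculation and to Data analyses, fixed before ADQ results are compared by arm. The timing matters because Study design and setting says that those who analyse the data will know the allocation.

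- **Preferred:** name one subscale as primary, or fix a test order. Test the first subscale at two-sided 5%, and the second at 5% only if the first is significant. Nothing in the article ranks IAC above SN, so the sponsor should choose the order and give the reason. State that the 5% error and about 80% power apply to the first subscale.
- **If the two are to stay equal:** use Holm. Restate the power as at least about 70% per subscale (about 75% to 77% if both true differences are 3 points), or about 81% to 91% for at least one subscale, and give the assumed correlation.

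Neither option needs more patients. The cost is that the second subscale can be claimed only after the first or, under Holm, that the stated power per subscale is less favourable than 80%. If 80% per subscale under a split error rate, or 80% joint power, is wanted instead, the sample size must rise as shown in the working.

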Notwithstanding, it is necessary to mention some of the limitations that can be linked to this study. First, the inclusion of caregivers with different relationships with patients (all possible dyads are included) can create non-homogeneity in the sample composition, as there may be specific relationship factors that influence the results. In addition, there may be a large loss of participants in the control group, that might not see any direct advantage in participating, so it may be strategic to remind them that they may require hospital-provided psychological support at the end of the study (albeit for a fee).

Despite these limitations, the results that are expected to be obtained after conducting this trial may be useful in helping patients-caregivers' dyads during the cancer care path to reduce possible disagreement within the dyads and enhance patients' adherence to cure and the satisfaction with the decision made and more in general to better their daily life.

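### 102 dyads fall slightly short of the plan's own target: 15% loss leaves fewer than the 88 completers required, and 44 per arm is just under 80% power for the named t-test

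*Protocol article*

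**What the plan says.** The section on sample size and power sizes the trial on the ADQ (Adherence Determinants Questionnaire), using two of its subscales, Interpersonal Aspects of Care and Subjective Norms. Its inputs are:

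- Difference: "we will observe a difference of 3 points in the average values of the two subscales IAC and SN".
- Spread: "A standard deviation of ~5 points is assumed for both subscales (untransformed values", "leading to a hypothesized effect size of 0.6".
- Test and error rate: a two-sample t-test with 1:1 allocation, "with a type I error of 5% (two-sided".

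From these it derives "a total of 88 patients (44 in the intervention group and the 44 in the control group", which "are required to provide 80% power to detect a difference ≥ 3 points". The last step is the allowance for loss: "Assuming a drop-out rate at 6-months of ~15%, a total of 102 patients will be required". No formula is printed for that step, and the text does not say whether 44 per arm came from a normal or a t calculation.

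Two other places bear on the point. The data analysis section excludes subjects who do not complete the later assessments, and the assessment schedule (Table 1) shows the ADQ only at T2.

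**The concern.** The section gives its inputs and its result, so a reader can check one against the other. If 88 completers are required and 15% of those enrolled are lost, the number enrolled has to leave 88 after the loss. 102 does not. Separately, the number of completers should deliver the stated power for the test the plan names, and 44 per arm appears to come from a formula for a different reference distribution. Both slips run the same way, towards too few patients.

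The loss is a real loss for the outcome used for sizing. A patient lost before T2 has no ADQ value at all, so earlier visits cannot stand in for it. What is at stake is whether the stated 80% power is delivered on the plan's own assumptions, and by how much it is missed if not.

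**Working it through.** **Inputs**, all from the sample size section: difference 3, SD about 5, so d = 3/5 = 0.6; two-sided α = 0.05; power 0.80; 1:1 allocation; drop-out about 15%.

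**1. Reproduce 44 per arm.** The normal approximation is n = 2(z₀.₉₇₅ + z₀.₈₀)²/d² = 2(1.960 + 0.842)²/0.36 = 43.60, rounded up to 44 per arm, 88 in total. This matches the plan exactly.

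**2. Solve for the named test.** The noncentral t solution for d = 0.6 is 44.59, rounded up to 45 per arm, 90 in total.

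| Completers per arm | Power, normal approximation | Power, two-sided t-test |
|---|---|---|
| 44 | 80.4% | 79.5% |
| 45 | 81.2% | 80.4% |

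**3. Check the allowance for loss.**

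- Completers left from 102 at 15% loss: 102 × 0.85 = 86.7, below 88.
- Enrolment needed for 88 completers: 88/0.85 = 103.5, so 104.
- Enrolment needed for 90 completers: 90/0.85 = 105.9, so 106.
- A route that gives the stated figure: 88 × 1.15 = 101.2, rounded up to 102. This is consistent with the text but is an inference. Another route is 44/0.85 = 51.8 per arm cut down to 51, which also gives 102. Either way fewer than 88 remain after a 15% loss.

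**4. Power delivered by 102 enrolled at 15% loss (t-test, d = 0.6).**

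- 43.35 per arm (86.7 in total): 78.9%.
- Nearest whole numbers, 43 and 44: 79.0%.

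The shortfall against 80% is about 1 percentage point. On the normal approximation, 43.35 per arm gives 79.8%, a shortfall of 0.2 points.

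**5. Loss that 102 can absorb.**

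- 88 completers: 1 − 88/102 = 13.7%.
- 90 completers: 1 − 90/102 = 11.8%.

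**The case against.** The strongest reply is that this is too small to matter. Both the drop-out rate and the SD are marked as approximate. With 86.7 completers, an SD of 4.93 instead of 5 restores 80% t-test power, while an SD of 5.5 gives 70.9% and one of 4.5 gives 86.6%. Uncertainty in the inputs is far larger than the slip, and two to four patients would change no design decision. That stands, and it sets the weight of the point. It does not make the figures agree: 15% is the loss the plan chose to allow for, and 102 does not cover it.

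It is also fair to say that the cause is unknown. Since no formula is printed, the text cannot be charged with multiplying by 1.15. What can be shown is that the result does not follow from the inputs.

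Three stronger readings are tempting and are not supported.

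- *The trial is underpowered in a serious way.* About 79% against 80% does not show that.
- *Power at 15% loss is 78.5%.* That is the value for 43 per arm, or 86 completers, which is a loss of 15.7%.
- *Unequal loss takes power well below this because the authors expect heavy control-arm loss.* The Discussion says only that "there may be a large loss of participants in the control group", as a possible limitation with a proposed mitigation, and it gives no rates. As an illustration under assumed losses of about 10% and 25%, 46 and 38 completers give 77.2%. But that is 84 completers, a total loss of 17.6%, and an even 42 and 42 already gives 77.6%. Nearly all of that drop comes from the greater total loss. With total loss kept near 15%, a split of 48 and 39 gives 78.6% against 79.0% for 43 and 44, so imbalance alone costs about 0.4 points.

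**Conclusion.** The point holds as a minor correction. The sample size section is inconsistent with its own inputs in two ways: 102 enrolled leaves 86.7 completers at 15% loss, fewer than the 88 it requires; and 88 completers give 79.5% power, not 80%, for the t-test it names. Taken together, 102 dyads give about 79% power at 15% drop-out, a shortfall of about 1 percentage point, or 2 patients (104) to 4 patients (106) in enrolment.

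This rests on the plan's own assumptions: d = 0.6, two-sided 5%, a t-test on one ADQ subscale, only completers analysed, and loss spread about evenly over the arms. Nothing elsewhere in the article repairs it, because the ADQ is measured only at T2 and non-completers are left out.

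**What to change.** Keep 102 dyads and correct the text of the sample size section so that it states what they deliver:

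- about 79% power (two-sided t-test, d = 0.6, one ADQ subscale) at 15% drop-out;
- 88 completers only if drop-out is at most 13.7%;
- at least 80% t-test power (90 completers) only if drop-out is at most about 11.8%.

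State how the allowance for loss was calculated, dividing by one minus the drop-out rate, and say that 44 per arm is a normal-approximation figure, with 45 for the t-test. If unequal loss between arms is discussed, give the rates and label them as an assumption.

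The cost is a few sentences and a slightly less favourable stated power. If the sponsor would rather keep the 80% claim at 15% loss, enrolment becomes 106, four dyads more.

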### Data analyses

Missing data: presence of missing data will be checked before conducting the main analyses. If a subject does not complete T1 and T2 he/she will be excluded from the analysis.

Normal distribution of continuous variables will be assessed (using skewness and kurtosis) before conducting the main analyses. Non-normal distribution will be handled by applying either non-parametric tests or SEM with an estimator for non-normal distribution.

Statistical analyses will be performed in SPSS version 25. Socio-demographic data collected in this study will be described in terms of mean, standard deviation, median, minimum, and maximum or reported frequencies in combination with confidence intervals. The preliminary analysis will be carried out through the Pearson or Spearman correlations r between the variables considered and by exploratory analysis of variance. To compare the two experimental and control groups, the *t*-tests (in case of normal distribution) or Mann-Whitney U tests (in case of non-existence of a normal distribution) will be applied, or cross tables with the chi-squared tests and (if necessary) the generalized exact Fisher's tests.

The main analysis will consist of an evaluation at different time-points of the psychometric scales, using linear models with mixed effects for repeated measures. The scales of interest will constitute the dependent variable, whereas the independent fixed factors will be the time of visit, the intervention group, the scale measured at baseline and the interaction term between the time of the visit and the intervention and, as a random effect, the patient. Multiple linear regressions will be calculated for both groups to evaluate the weight of each variable on the main outcome.

The semi-structured interviews will be analyzed by NVivo v10, a qualitative data analysis software.

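### The rule excluding subjects who do not complete T1 and T2, read naturally, discards usable data from randomised patients and can bias the arm comparison if loss relates to outcome

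*Protocol article*

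**What the plan says.** The missing-data paragraph of Data analyses states: "If a subject does not complete T1 and T2 he/she will be excluded from the analysis". The same section describes the main analysis as an evaluation of the psychometric scales over time, "using linear models with mixed effects for repeated measures", with visit, arm, their interaction and the baseline score as fixed terms and the patient as a random effect.

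Table 1 and the measures sections fix when each scale is collected. HADS, MSPSS and SF-12 are taken at T0, T1 and T2. SDM-Q-9 and CARE are taken at T0 and T1 only. ADQ, the outcome used for the sample size, is taken at T2 only.

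Among its limitations, the Discussion says that "there may be a large loss of participants in the control group, that might not see any direct advantage in participating". It gives no rate, and the countermeasure is a reminder that paid support can be requested after the study. The sample-size section makes one overall allowance: "Assuming a drop-out rate at 6-months of ~15%, a total of 102 patients will be required".

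**The concern.** The exclusion is stated outright, so it is not a detail left to a fuller document. It acts after randomisation and depends on attendance, which the article itself suggests may differ by arm. It also works against the chosen model. A mixed model for repeated measures can take a patient with one of two follow-up visits, and its estimates are valid when missingness depends only on observed data. Deleting such patients first gives up that advantage.

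Two things are at stake. One is precision, because observed values are thrown away. The other is the randomised comparison: patients who attend both visits are a selected group, and if selection differs by arm and relates to outcome, the arms are no longer comparable.

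**Working it through.** **1. The plan's own figures.** Inputs from Sample size and power calculation: difference 3, SD 5, two-sided 5%, power 80%.

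- n per arm = 2 × (1.960 + 0.842)² × (5/3)² = 43.6, rounded up to 44, so 88 in total. This reproduces the plan. Exact t-test power at 44 per arm is 79.5%.
- 88 × 1.15 = 101.2, rounded up to 102, which reproduces the stated total. Dividing instead gives 88 / 0.85 = 103.5, or 104.
- Expected number with T2 at 15% loss: 102 × 0.85 = 86.7.

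The allowance covers numbers. It does not address who is lost or from which arm.

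**2. What the rule removes, by attendance pattern** (visits from Table 1; rule read as missing either visit).

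| Attended | Observed follow-up values that the rule discards | ADQ |
|---|---|---|
| T1 and T2 | none | kept |
| T1 only | T1 HADS, MSPSS, SF-12, SDM-Q-9, CARE | never observed, whatever the rule |
| T2 only | T2 HADS, MSPSS, SF-12 | observed, then discarded |
| neither | none exist | never observed |

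For SDM-Q-9 and CARE, a T1-only patient has complete follow-up, yet is dropped for missing a visit at which those scales are not given. For ADQ, a T2-only patient has the full outcome, yet is dropped for missing a visit at which ADQ is not given.

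If the rule means missing both visits, only the last row is excluded and nothing observed after baseline is lost.

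**3. Cost to ADQ from the rule itself.** If a share m of patients with T2 missed T1, the rule discards m × 86.7 ADQ values, or about 0.87 per percentage point. The article gives no value for m.

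**4. Unequal loss and power, as illustration.** These arm-specific rates are assumptions; only the overall 15% is in the article. With 51 randomised per arm and effect size 0.6, t-test power is:

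| Loss, experimental / control | Patients left | Power |
|---|---|---|
| 15% / 15% | 43.4 / 43.4 | 78.9% |
| 10% / 20% | 45.9 / 40.8 | 78.7% |
| 5% / 25% | 48.4 / 38.2 | 78.3% |
| 10% / 30% | 45.9 / 35.7 | 75.7% |
| 10% / 40% | 45.9 / 30.6 | 71.8% |

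With overall loss held at 15% (first three rows), imbalance alone barely changes power.

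**5. Unequal loss and bias, as illustration of missing T2 data in general, not of this rule.** In one arm, completer mean minus full-arm mean = d × D, where d is the share lost and D is the completer mean minus the dropout mean. With the same D in both arms, the arm difference (experimental minus control) shifts by (d_exp − d_ctrl) × D. Assume D = 2.5 to 5 points (0.5 to 1 SD):

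- 15% / 15%: 0.
- 10% / 20%: −0.10 × 2.5 to −0.10 × 5 = −0.25 to −0.5 points.
- 10% / 30%: −0.20 × 2.5 to −0.20 × 5 = −0.5 to −1.0 points.

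If dropouts score higher than completers, the signs reverse. If D = 0, there is no shift however unequal the loss. The article gives neither D nor the split by arm.

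**The case against.** The strongest reply is that the sentence is ambiguous. If only subjects missing both visits are excluded, partial completers stay in and little is lost. That is a fair possible reading, but the text does not settle it, and missing either visit is the more natural sense. The sentence needs rewriting on both readings.

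A second reply concerns ADQ. A reader might infer that the rule biases the ADQ comparison by a calculable amount or raises its type I error. The documents do not support that. ADQ has no T0 or T1 value, so a patient without T2 has no ADQ under any rule, and removing the sentence would not restore one. Such bias would come from missing T2 data, and its handling may be set out in a fuller document. It would also rest on assumed dropout rates and on an assumed link between dropout and outcome. This reply stands. For ADQ, the rule's own effect is confined to patients with T2 but no T1.

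Third, a reader might say that the article expects heavy control-arm loss. It says only that there may be one, and the reason offered (no direct advantage) relates to allocation, not to how the patient is doing. Unequal loss without a link to outcome does not bias the contrast. This also stands. What remains is that the authors foresee arm-related loss while fixing a rule that discards partly observed patients.

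**Conclusion.** The point holds in a limited form. On its natural reading, the rule turns the analysis into a completers-only comparison and discards observed follow-up data that the planned analyses could use. The loss of information is certain for every patient seen at only one follow-up visit. Bias is conditional: it needs loss that differs by arm or in its relation to outcome, and the article does not allow its direction or size to be determined. The power and bias figures above are illustrations under assumed rates and gaps, and the bias figures describe missing T2 data in general. If the authors meant missing both visits, the harm is largely absent and a clearer sentence suffices.

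**What to change.** Replace the exclusion sentence with wording such as:

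> All randomised dyads are analysed in the arm assigned. Mixed models use every available T1 or T2 value. ADQ is analysed in every patient with T2 data, whatever their T1 status. A completers-only analysis is supplementary.

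Report attrition by arm and visit. Add one simple sensitivity analysis for missing T2 ADQ, for example delta-adjusted imputation from a small set of T0 and T1 variables; with 51 patients per arm, the imputation model should stay small.

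This needs no new data, visits or participants. The cost is a change of wording and a little more analysis work. It should be settled before outcomes are examined by arm.
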